## Methods and analysis

### Study design

This study is a single-center, open-label, multiparallel group, randomized controlled trial. The study consists of two intervention periods: [1] under habitual diet conditions and [2] under balanced standard meal conditions. After a 3-day experiment run-in period, a total of 32 subjects (16 males and 16 females) will be randomized into one of 4 arms in 1:1:1:1 ratio (Figure 1). The 4 arms will include soy powder and milk powder which will be completely dissolved in 250 ml water, almond snacks with 250 ml of water, and a control arm (250 ml of water). Test days will be scheduled before and after the two intervention periods to assess the potential effects of premeal snacks under the habitual diet and standard balanced diet patterns, respectively. During the entire period of this experiment, subjects will be asked to complete a food recording diary (online) including the type, amount, and time of all meals, snacks, and drinks except water (in the form of photos and text). Physical activity and sleep will also be recorded via a mobile app for step count and sleep time records. The study will be performed at Wenzhou Medical University. The protocol followed the Standard Protocol Items: Recommendations for Interventional Trials statement (27).

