### Intervention

This study consists of a baseline blood glucose assessment day (D2) under habitual diet conditions (before the start of the intervention, V1), two intervention periods under two different diet patterns with equal experimental days (D3-D6, D10-D13), and a standard balanced meal run-in period between the two intervention periods (D7-D9). A 3-day experiment run-in period will be set before Visit 1 (V1). During this period, all subjects will be asked to maintain their habitual eating without energy restrictions and maintain a regular daily schedule. In addition, they will not be allowed to smoke, drink, or perform vigorous exercise in the course of this trial. All subjects will wear continuous glucose monitoring (CGM) to monitor dynamic interstitial glucose in the mornings of V1. The first intervention period will be under the habitual diet condition from D3 to D6 (4 days), during which all subjects will be asked to maintain their habitual eating and daily activities, similar to the experimental run-in period. After the first intervention period, a 3-day standard balanced meal run-in period from D7 to D9 will be performed before the second intervention to ensure that the standard meals are tolerable to the individual participants. The second intervention will consist of prelunch snacks with standard meals that had the same macronutrient composition as those in the run-in period. Screening will be finished within 1 week before the experiment (V0). Randomization will be performed after the completion of screening. Outcomes will be assessed after the two intervention periods. Blood samples will be taken before and after the two intervention periods (V1-V4), and interstitial glucose will be monitored throughout the 2 week experimental period. An overview of the study visits is presented in Table 2. During the entire period of this experiment, subjects will be asked to complete a food recording diary (online) including the type, amount, and time of all meals, snacks, and drinks except water (in the form of photos and text). Subjects will be supervised daily by the researcher in charge to ensure their food diaries are uploaded on time. Physical activity and sleep will also be recorded via a mobile app for step count and sleep time records.

**Table 2 T2:** Overview of study visits.

**Visit**	**V0**	**V1**	**V2**	**V3**	**V4**
Time from the start of wearing CGM^a^	−7	1	7	10	14

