### Standard balanced meals run-in period

A 3day run-in period will be scheduled between Visit 2 (V2) and Visit 3 (V3), during which subjects will be asked to maintain the same levels of rest and physical activity as they did during the experimental period. Subjects will be given standard balanced meals 3 times per day during the run-in period and will not be provided with premeal snacks. Furthermore, researchers will train the subjects to eat in the same fixed meal order and have a similar duration of each meal (to keep a similar chewing pace) to control for confounding factors.

Standard balanced nutrients will be given for each meal during the second intervention period. Calories will be matched between groups for each meal and a total 24-h period within participants. Energy requirements for the day will be divided by sex calculated with the participants' average using the Harris-Benedict formula (29).

Males: resting metabolic rate (kcal/d) = 66.5 + (13.75 × weight in kilograms) + (5.003 × height in centimeters) − (6.775 × age in years);

Females: resting metabolic rate (kcal/d) = 665.1 + (9.563 × weight) + (1.850 × height) − (4.676 × age).

The energy allocation will be 30, 40, and 30% for breakfast, lunch, and dinner, respectively, with macronutrient ratios following the dietary guideline recommendations of 50–55% of calories from carbohydrates, 15–20% from protein, and 25–30% from fat. Daily meals will include vegetables, meat, and staple foods. After this trial, we will upload the realistic standard meals in the form of a photograph. The types of food are shown in Table 4.

**Table 4 T4:** Food types of standard meals.

**Food type**	**Staple food**	**Vegetable**	**Protein**
Breakfast	Noodles	Tomato	Egg
	Bread	Cucumber	Milk
	Rice	Cabbage	Pork
Lunch and dinner	Rice	Broccoli	Fish
		Cabbage	Chicken
		Carrot	Pork
		Mushroom	Egg
		Tomato	

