### Comparisons

First, the three intervention arms will be combined as a group and compared with the control group to evaluate whether the premeal intervention could improve GV. Second, the two arms with high-protein snacks will be combined as a group and compared with the control group; moreover, the high-fat snack arm will be compared with the control group to evaluate whether the two snacks (high-protein and high-fat snacks) could improve GV. If both the high-protein and high-fat snacks show significant improvement effects, we will further directly compare the high-protein snack (combining milk powder and soy powder into one group) with the high-fat snack (almonds) interventions to evaluate which is better. Third, we will also compare the milk powder group with the control group and the soy powder group with the control group, and if both high-protein snack groups show significant improvement, we will further compare the animal protein and plant protein groups directly to verify whether the plant protein group is similar to the animal protein group. Finally, we will compare all the results from different dietary patterns to determine whether premeal snacks have similar effects under habitual diet and standard balanced meals.

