Another important advantage of the trial is that we will implement a premeal snack intervention under two different dietary conditions. Several studies have reported the beneficial effects of premeal snack interventions on glucose metabolism under well-controlled dietary patterns (14, 40, 42). Although the effects observed in this way are significant, such studies under well-controlled conditions could not represent the full extent of this benefit in real daily diet because GV itself can vary with the order of meals, macronutrient ratios, and the interval between meals (11). The purpose of this design is to determine whether the intervention, when applied to a daily diet, will result in improvements similar to those obtained under the experimental control diet. First, before the start of the experiment, we will set a run-in period with the aim of testing the baseline GV levels of the subjects as their own control. After the run-in period, the first period of the intervention will begin, and premeal snacks will be given under exactly the same habitual diet conditions as those in the run-in period, during which no restrictions will be imposed on the amount and type of food consumed by the subjects at their regular meals. After the end of the first intervention period, a standard balanced meal run-in period will be set to ensure that the subjects' metabolism adapts to this meal pattern before the start of the second intervention period, to obtain more stable data for the second-period results.

Notably, as the prediabetic population continues to expand, the solution to reduce the risk of the development of diabetes in this population is an urgent issue. It has been reported that in the process of disorders in glucose metabolism, the increase in postprandial glucose excursion and delayed duration of postprandial glucose excursion occurs earlier than the increase in FBG levels in patients with prediabetes (43). Our study will select subjects from the pre-diabetic population aim to alleviate glucose metabolism and achieve prevention through simple and easily implemented lifestyle interventions. In addition, the results from the prediabetic population are more likely to be extrapolated to diabetic populations.

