In conclusion, this is the first RCT protocol that directly compares the effects of different natural snacks under different dietary patterns on GV. We will carry out a careful and rigorous research protocol for the following three issues we want to study: [1] the comparison of GV improvement effects between high-protein snacks and high-fat snacks; [2] the comparison of GV improvement effects between animal-based high-protein snacks and plant-based high-protein snacks; and [3] the comparison of the effects under two different dietary patterns. The limitation of this study is that we will use nuts eaten with water instead of nut powder solution. Because the high-fat powder solution does not have good compliance, we will consider the acceptability of the subjects. Therefore, there may be confounding factors caused by chewing activities in the whole nut group. In addition, the number of people included in this study will be quite small, so the conclusions should be extrapolated with more people. Another limitation of this study is the short duration of the experiment, with only 4 days per period. This is because the maximum validity of a single CGM device is only 14 days. Therefore, the effects we derive will represent only acute effects, and more long-term anthropometric and metabolic outcomes will need to be validated with longer-term experiments.

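### Diet order is the same for everyone and no between-period contrast is named, so the plan can estimate, but not determine, whether snack effects are similar under the two diets

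*Protocol article*

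**What the plan says.** The trial is a "single-center, open-label, multiparallel group, randomized controlled trial" with four arms: soy powder, milk powder, almonds and water. Snack arm is the only randomised factor.

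Under Intervention, all participants follow their habitual diet on D3-D6. Then "a 3-day standard balanced meal run-in period from D7 to D9 will be performed before the second intervention". For D10-D13, "The second intervention will consist of prelunch snacks with standard meals". No snacks are given on D7-D9. In that run-in, "researchers will train the subjects to eat in the same fixed meal order" and to keep a similar meal duration.

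The continuous glucose monitoring section takes D2 and D9 as the two period baselines and drops D1, D3, D10 and D14.

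The last step of Comparisons is to "compare all the results from different dietary patterns to determine whether premeal snacks have similar effects" under the two diets. The closing paragraph of the Discussion lists this as the third of three issues under study. The limitations given there are chewing in the almond arm, small numbers and short periods. Fixed diet order is not among them.

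The Statistical analysis plan section names paired t-tests within groups, ANOVA and Dunnett's test between groups, non-parametric alternatives, and two-sided 0.05.

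**The concern.** Two problems meet in one declared aim.

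The first is design. Diet and period coincide for every participant, so the between-diet difference in snack effect is also a between-period difference. Anything that alters the snack effect over time in the snack arms alone is counted as a diet effect. Candidates are four earlier days of snacks, habituation, and a D9 baseline still shifted after only three snack-free days. Meal-order and pace training also arrives with the standard meals, so a difference would belong to that whole package and not to meal composition alone.

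The second is analysis. No named test addresses the difference in effects between periods. Placing two sets of period results side by side invites two errors: taking significance in one period only as a difference between diets, and taking two non-significant results as similarity. Either error would produce a diet-pattern conclusion that the data do not carry.

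**Working it through.** **The plan's own figure.** Sample size determination gives 6 per group and 20% dropout: 6/0.8 = 7.5, rounded up to 8, and 4 × 8 = 32. This step reproduces. The section gives no SD, margin, power or between-period correlation, and the size is not set for the diet comparison.

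**Assumptions for the check.** Change scores have SD 1 in each period. The true snack effect is identical in both periods, at 1 or 1.5 SD. The within-person correlation r between the two periods' change scores is 0, 0.5 or 0.8. Each period is tested by a two-sided t-test at 0.05. None of these effect sizes or correlations comes from the article. The sample sizes do: 8 v 8 is one snack arm against water, and 24 v 8 is the three snack arms pooled (3 × 8) against water, the first step in Comparisons. The pooled case assumes that all three snacks have the same effect.

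**Discordant significance (one period significant, the other not).** At r = 0 it is 2p(1 − p), where p is the power in one period:
- 8 v 8, 1 SD: p = 0.461, so 2 × 0.461 × 0.539 = 0.50
- 8 v 8, 1.5 SD: p = 0.797, so 2 × 0.797 × 0.203 = 0.32
- 24 v 8, 1 SD: p = 0.659, so 2 × 0.659 × 0.341 = 0.45
- 24 v 8, 1.5 SD: p = 0.945, so 2 × 0.945 × 0.055 = 0.10

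For r above 0 the figures come from 40,000 simulated trials per setting:

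| Comparison | Effect | r = 0 | r = 0.5 | r = 0.8 |
|---|---|---|---|---|
| 8 v 8 | 1 SD | 50% | 34% | 21% |
| 8 v 8 | 1.5 SD | 32% | 23% | 15% |
| 24 v 8 | 1 SD | 45% | 31% | 19% |
| 24 v 8 | 1.5 SD | 10% | 9% | 6% |

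In the same simulations, a direct t-test of the within-person period differences (snack against water) rejects in 5% of trials, as it should.

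**Precision of the difference in effects.** The 95% CI half-width is t(0.975, n1 + n2 − 2) × √[(1/n1 + 1/n2) × 2(1 − r)]:
- 8 v 8 (t = 2.145): 2.145 × √(0.25 × 2) = 1.52 SD at r = 0; 1.07 at 0.5; 0.68 at 0.8
- 24 v 8 (t = 2.042): 2.042 × √(0.1667 × 2) = 1.18 SD at r = 0; 0.83 at 0.5; 0.53 at 0.8
- 6 v 6, after the planned dropout: 1.82, 1.29 and 0.81 SD

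At 8 v 8 and r = 0.5, an observed difference of zero would be compatible with a between-diet change of 1.07 SD either way, which is as large as an entire 1 SD snack effect.

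**What cancels and what does not.** In (snack minus water) for period 2 minus (snack minus water) for period 1, anything that shifts all arms equally drops out, including sensor age and calendar time. What remains is any change in the snack effect itself, whether caused by diet, by order, or by a D9 baseline still shifted in the snack arms only.

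**The case against.** The strongest reply has four parts.

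*The article condenses a fuller plan.* A model and a contrast are often left to the analysis plan, and nothing printed rules out an arm-by-period test. This stands: a missing test alone would be a weak point. The fixed order, however, is explicit in the design, and so is the promise to determine similarity.

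*The text never says that p-values will be compared.* Correct. A reader might infer it from the significance-gated steps in Comparisons, but those govern snack-versus-snack comparisons, and the wording on separate assessment by period sits under Secondary outcomes. The misreading is a risk, not a stated rule.

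*Fixed order does less harm than it seems.* A reader might infer that sensor age or elapsed time biases the trial, or that snack-versus-control is itself distorted. The documents do not support that: a water control runs in both periods, D9 gives a new baseline, and D10 is dropped. The three snack-free days also reduce carry-over, though they cannot exclude it. Nor is the Discussion's remark that "GV itself can vary with the order of meals" an admission of bias. It explains why controlled conditions may not represent daily eating, and meal training is arguably part of the standard-meal condition.

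*The numbers depend on assumptions.* They do. The 50% figure needs a 1 SD effect and zero correlation, and the pooled comparison at 1.5 SD falls to 6-10%. A reader might also conclude that similarity could never be shown at this size. That depends on a margin and a correlation that the article does not give.

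**Conclusion.** The point holds in a limited form. The trial can estimate how the snack effect differs between period 1 and period 2. It cannot attribute that difference to diet pattern apart from order and prior exposure, or to meal composition apart from the accompanying training. The snack-versus-control comparisons within each period stand.

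Under the stated assumptions, reading significance period by period would suggest a difference that does not exist in about 15-50% of trials for a single arm and 6-45% for the pooled arms, against 5% for a direct test. The difference in effects would carry a half-width of 0.68-1.52 SD or 0.53-1.18 SD with no dropout, so a non-significant contrast would not show similarity. Because this is one of three declared questions, the analysis and wording should change.

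**What to change.** Replace the last sentence of Comparisons with one prespecified exploratory contrast for change in MAGE: (snack minus control) in period 2 minus (snack minus control) in period 1. Take it from a repeated-measures model with arm, period, arm-by-period, period baseline and sex, and report it with a 95% CI. Promise to estimate the difference in effect between the two periods instead of determining whether the effects are similar.

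Add to the limitations that diet pattern is confounded with order and prior snack exposure, that meal-order and pace training came with the standard meals, and that a non-significant contrast does not show similarity.

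If arms are compared on D8-D9, when no snacks are given, report the estimate and CI descriptively. At 8 per arm it should not serve as a pass/fail test of carry-over.

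The contrast resolves the side-by-side reading but not the confounding, which only the wording can address in this design. The cost is one model and a few sentences, with no change to visits, sample size or intervention. The downside is a weaker diet-pattern claim.

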### Statistical methods

#### Sample size determination

The mean amplitude of glycemic excursions (MAGE) was chosen as the primary outcome indicator and it is expected that the MAGE will be reduced by 20% based on a study by Imai (33). Using PASS software (version 11.0), a sample size of 6 participants per group is required using the non-inferiority test for comparison of sample means. Assuming a 20% dropout rate, the sample size required for this study is 8 participants for each group.

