#### Statistical analysis plan

All parameters will be assessed for normality using the Kolmogorov-Smirnov test, and homogeneity of variance will be tested using the Levene test. Descriptive statistics will be expressed as the mean ± standard deviation (SD) for normally distributed data and as the median (Q1-Q3) for non-normally distributed data. Mean changes in parameters within the group will be assessed by calculating the difference between pre and postintervention measurements. When the data are normal and the variance is equal, paired *t*-tests will be used to assess the effect of interventions. Differences between groups will be assessed using the variance ANOVA test. Dunnett's test will be used to determine whether there is a significant difference between the experimental and control groups. When the assumptions for parametric tests are not met in the data, non-parametric statistical methods will be used.

Subgroup analyses by sex will be performed to explore whether the effect is modified by sex. The correlations between physiological factors and blood glucose levels will be assessed by Pearson's or Spearman's correlation analysis. Some *post-hoc* exploratory analyses will also be conducted. All analyses will be performed using SPSS version 24.0 (SPSS Inc. Chicago, IL, USA). The criterion for statistical significance will be a two-tailed *p* < 0.05.

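### The 6 per group is sized by a non-inferiority test that the planned analysis does not contain, and it does not support the single-arm Dunnett comparisons that decide whether soy and milk are compared at all

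*Protocol article*

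**What the plan says.** All references are to the protocol article.

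- **Sample size determination.** MAGE is the sizing outcome and "it is expected that the MAGE will be reduced by 20" per cent. The paragraph states that "a sample size of 6 participants per group is required using the non-inferiority test for comparison of sample means". Then: "Assuming a 20% dropout rate, the sample size required for this study is 8 participants for each group". The paragraph does not say which two arms the test compares.
- **Study design.** Participants "will be randomized into one of 4 arms in 1:1:1:1 ratio", 32 in total.
- **Introduction and Discussion.** Both state the hypothesis that the plant-protein snack (soy) is non-inferior to the animal-protein snack (milk) on glycemic variability.
- **Statistical analysis plan.** Within-group change is assessed by paired t-tests and between-group differences by ANOVA. Dunnett's "test will be used to determine whether there is a significant difference between the experimental and control groups". Non-parametric methods are the fallback. "The criterion for statistical significance will be a two-tailed" p < 0.05. No non-inferiority test is listed.
- **Comparisons.** The order is: three snack arms pooled against control; the two protein arms pooled, and almonds, against control; then milk and soy each against control. Only if both protein arms show significant improvement are they compared with each other. The aim of that last step is to verify that they are similar, with no non-inferiority rule.

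**The concern.** The sizing paragraph and the analysis section both commit to a method, and the methods differ. A sample size belongs to one test, effect and error rate. Here the number comes from a non-inferiority comparison of two means, while the analysis consists of two-sided difference tests, with a multiplicity-adjusted test for each snack against control.

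Two things are at stake. First, saying that 6 per group is required tells the reader that the trial is adequately powered, so a snack arm that misses significance against control may be read as having no effect. Second, significance against control is also the condition for comparing soy with milk. If the single-arm tests have modest power, the hypothesis that appears to have set the sample size may never be examined.

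**Working it through.** **1. The plan's own figures.** Dropout: 6 / (1 − 0.20) = 7.5, rounded up to 8; 4 × 8 = 32. Both reproduce. The 6 itself cannot be reproduced forward, because the article gives no margin, SD, power or sizing alpha. An article may leave these to a fuller document, so their absence is not the point here. It only means that the 6 has to be worked backwards.

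**2. What 6 per group implies for a non-inferiority t-test.** Let d = (margin − true difference) / SD. Power = P(T > t(1−α, 10)), with T noncentral t on 2 × 6 − 2 = 10 df and noncentrality d / √(2/6). Assuming 80% power:

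| One-sided α | Critical t | d |
|---|---|---|
| 0.05 | 1.812 | 1.54 |
| 0.025 | 2.228 | 1.80 |

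**3. Single-arm Dunnett power at the same standardized distance.** The bridging assumption is that the snack-versus-control effect, in SD units, equals d. The two-sided 5% Dunnett critical value for three arms against control, by simulation, is 2.54 (6 per arm, df 20) and 2.48 (8 per arm, df 28). Noncentrality is d / √(2/n): for d = 1.54 this is 2.67 at n = 6 and 3.09 at n = 8; for d = 1.80 it is 3.11 and 3.59.

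| d | Dunnett per arm, 6 completers | Dunnett per arm, 8 completers |
|---|---|---|
| 1.54 | 56% | 72% |
| 1.80 | 71% | 86% |

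**4. The gate.** Soy and milk are compared only if both beat control. With both true effects equal to d, and allowing for the shared control arm and shared error variance (simulation), both pass Dunnett with this probability:

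| d | 6 completers | 8 completers |
|---|---|---|
| 1.54 | 41% | 59% |
| 1.80 | 58% | 77% |

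**5. The other planned tests at the same d, 6 per arm.**

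| Test | d = 1.54 | d = 1.80 |
|---|---|---|
| Three snack arms pooled vs control (18 vs 6) | 88% | 95% |
| Two protein arms pooled vs control (12 vs 6) | 84% | 93% |
| ANOVA, one arm differing by d | 70% | 84% |
| Unadjusted two-sided t-test, one arm vs control | 67% | 80% |

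The pooled contrasts use the four-arm error variance (df 20).

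**6. Taking the 20% as the effect against control.** In SD units the effect is 20% divided by the SD as a percentage of mean MAGE. The article gives no SD, so a range is assumed:

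| Assumed SD, % of mean MAGE | Effect in SD units | Dunnett, n = 6 | Dunnett, n = 8 |
|---|---|---|---|
| 10 | 2.00 | 81% | 93% |
| 15 | 1.33 | 43% | 58% |
| 20 | 1.00 | 24% | 33% |

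**7. Differences detectable with 80% power (two-sided 5%).** One arm against control under Dunnett: 1.97 SD with 6 completers, 1.67 SD with 8. All snacks against control: 1.39 SD (18 vs 6), 1.18 SD (24 vs 8).

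**The case against.** The strongest reply is that non-inferiority is no stray method here. Soy-versus-milk non-inferiority is a declared hypothesis, a direct comparison of the two is planned, and the 6 may have been meant for that comparison alone. This stands as far as it goes: the fault is that the hypothesis was not carried into the analysis. It does not rescue the figure, because the planned comparison is conditional on two significance tests, asks about similarity, and has no non-inferiority rule.

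Three stronger readings are tempting, and the document supports none of them.

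- *That the planned tests in general are underpowered.* At the matched effects the pooled contrasts against control, which come first in the Comparisons section, have 84–95% power. ANOVA (84%) and the unadjusted t-test (80%) also keep up if the sizing used one-sided 0.025.
- *That Dunnett power is inadequate whatever SD and margin were used.* The soy-versus-milk distance to the margin and the snack-versus-control effect are different quantities. Take an assumed margin of 10% of mean MAGE, no true difference, and SD 6.5%: 10 / 6.5 = 1.54, so the non-inferiority test has 80% power at 6. A 20% reduction against control is then 20 / 6.5 = 3.1 SD, and Dunnett power exceeds 99%. An SD of 10% already gives 81%.
- *That the 6 was miscalculated.* The only step that can be checked, the dropout inflation, is correct.

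The Discussion does concede that the sample is quite small, but as a caution about extrapolation. It does not withdraw the statement that 6 per group is what is required.

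**Conclusion.** The point holds in a limited form. The stated size comes from a test that the analysis section does not include, so it is not the size for the planned analysis and does not justify the single-arm Dunnett comparisons.

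At an equal standardized distance, those comparisons fall below the 80% assumed for the sizing: by 24 or 9 percentage points with 6 completers (80 − 56 and 80 − 71). With all 8 retained, the shortfall remains only under one-sided 0.05 sizing (72%); under 0.025 the power is 86%. The joint gate on soy and milk stays below 80% in all four cases (41–77%).

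These figures rest on an assumed sizing power of 80%, the two sizing alphas shown, and equality of the two standardized effects. They show that the justification is missing; they do not establish the trial's actual power, which depends on an SD that the article does not give. The point should be addressed, but it does not call for a larger trial.

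**What to change.** Keep 32 participants and make the sizing and the analysis agree, by one of two routes.

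- **(a)** Add the soy-versus-milk non-inferiority test to the statistical analysis plan, with its margin and a confidence-limit decision rule. Remove the condition that both arms first beat control, and say that the 6 per group applies to that comparison only.
- **(b)** Delete the statement that 6 per group is required by a non-inferiority test.

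Route (a) keeps the hypothesis in the Introduction and Discussion connected to a test; route (b) leaves it without one.

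Under either route, state what the trial can detect with 80% power under the planned tests: about 1.67 SD for each snack against control under Dunnett with 8 per arm (1.97 SD with 6 completers), and about 1.18 SD for all snacks against control (1.39 SD at 18 vs 6).

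The cost is one rewritten sample size paragraph and, for (a), a short addition to the analysis section and a changed condition in Comparisons. The stated figure becomes less favourable. No extra participants are needed.
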